### 7.3. Endpoints

The principal endpoint will be vital status (dead/alive) at day 28

The secondary endpoints will be

- day-90 mortality
- number of ventilator-free days at day 28
- number of renal replacement therapy-free days at day 28
- number of vasopressors-free days at day 28
- use of ECMO before day 28
- value of the SOFA score at days 7, 14 and 28 [1] (see appendix A).
- changes in SOFA scores over the following 7, 14 and 28 days
- value of the SARS-CoV-2 viral load, expressed as cycle threshold, [2] in the tracheal aspirates (for intubated patients) or nasopharyngeal swabs (for extubated patients) at days 7, 14 and 28
- blood C reactive protein (CRP) concentrations at days 7, 14 and 28
- length of stay in the acute care hospital
- location of the patients at day 90: acute care hospital, post-acute care hospital, long-term residency, home
- WHO progression scale prior transfusion, at day 7 and at discharge (see appendix B)
- Hospital Activity of Daily Living (ADL) functional score at day 90 and at day 365. [3] (see appendix C).
- Anxiety-depression evaluation scale at day 90 and at day 365. [4] (see appendix D ).
- Quality of life scale (EQ-5D-5L) at day 90 and at day 365. [5] (see appendix E).
- Transfusion-related adverse events within 7 days
- Sero-positivity to SARS-CoV-2 at days 1, 7, 28 and 90
- Adverse events related to standard of care (mechanical ventilation, prolonged decubitus, prone positioning...) such as:
  - o Ventilator associated pneumonia
  - o Secondary bacteremia [6]
  - o Deep vein thrombosis and pulmonary embolism
  - o Pressure ulcers, stage 2 to 4 (*i.e.* loss of skin, of tissue or of bone) [7]
  - o Ventilator induced baro-traumatism (pneumothorax, pneumo-mediastinum, sub-cutaneous emphysema) [8]
  - o Accidental ablation of tracheal or vascular device [9]
  - o Ventilator induced baro-traumatism (pneumothorax, pneumo-mediastinum, sub-cutaneous emphysema) [8]
  - o Accidental ablation of tracheal or vascular device [9]

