### 7.2. Secondary

The secondary objectives are to assess:

- the efficacy of convalescent plasma
  - o to reduce day-90 mortality
  - o to reduce the duration of mechanical ventilation over the 28 days after inclusion,
  - o to reduce the severity of organ failure over the 28 days after inclusion,
  - o to reduce the use of organ support over the 28 days after inclusion
  - o to reduce the viral load, expressed as cycle threshold, over the 28 days after inclusion
  - o to reduce the intensity of the inflammatory response during the 28 days following inclusion.
  - o to reduce the acute care hospital length of stay
  - o to increase the functional, psychological state and quality of life at day 90 and at day 365 after inclusion
  - o to assess the impact of convalescent plasma on sero-conversion against SARS-CoV-2
- the incidence of adverse events related to plasma transfusion
- the incidence of adverse events related to organ support.

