#### **9.5.4.10 Discharge from the hospital**

- Date of ICU discharge
- Patient alive (Y/N)
  - If Yes :
    - Date of last extubation
    - Destination (Home, revalidation, acute care unit)
- 
- Tracheostomy during the ICU stay
  - Y/N
  - date
- Date of hospital discharge

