### **9.5.5 Data to be shared at the European level regarding convalescent plasma use**

[https://ec.europa.eu/health/blood\\_tissues\\_organs/covid-19\\_en](https://ec.europa.eu/health/blood_tissues_organs/covid-19_en)

Register:

[https://ec.europa.eu/health/sites/health/files/blood\\_tissues\\_organs/docs/guidance\\_plasma\\_covid19\\_en.pdf](https://ec.europa.eu/health/sites/health/files/blood_tissues_organs/docs/guidance_plasma_covid19_en.pdf)

- Gender, age range (30-39, 40-49 etc.), co-morbidities
- Transfusion time point (in days from disease onset)
- Number, volume and anti-body titre of transfused unit(s)
- Therapies administered to the patient in parallel (other than supportive care)
- Clinical symptoms and laboratory parameters– according to the disease progression scale (Appendix B) at the following time points:
  - Prior to transfusion

- 5 days after transfusion
- At discharge (if the patient survives)
- Any serious adverse reactions or events possibly linked to the transfusion
- Length of hospitalisation (if no death).

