## 9.9. Statistical Analysis

- Primary outcome

The primary outcome of the trial is mortality at day 28. Based on prior reports from China, Italy and UK, and consistent with personal observations, we anticipate that the mortality at day 28 will be around 40 %. As no comparative study has yet been published, the reduction that we anticipate is empiric. We consider that a one third relative reduction in 28-day mortality is realistic and clinically relevant. As this reduction might be greater, we plan to perform an interim analysis for ethical reasons. With a two-sided  $\alpha$ -risk of 0.05 and a  $\beta$ -risk of 0.20, the minimal number of patients to include to reach significance for a one third relative reduction in 28-day mortality (an absolute reduction of 13.5% day-28 mortality in the intervention group assuming a day-28 mortality of 40 % in the control group) is 250 in the control group and 250 in the active group (total number of patients = 500). This number allows for four interim analyses to be performed in addition to the final analysis, respectively after assessment of 100, 200, 300, 400 and 500 patients. Considering that others trials in COVID-19 may result in modification in mortality and therefore in standard of care, we anticipate that the number of patients that is necessary to address our hypothesis may vary, and will have to be adapted depending on the results of the interim analyses.

- Statistical analysis plan

Results will be analysed in intention to treat and expressed as means and standard deviations (SD) for quantitative variables with a Normal distribution and as medians and 25th to 75th percentiles for skewed distributed quantitative variables. Qualitative variables will be expressed using counts and percentages.

Mean values between groups will be compared by Student t-test but also by the non-parametric Wilcoxon test when normality assumption is not fulfilled. Proportions will be compared by the chi-square

test. Appropriate multivariate analyses will be performed to assess the relationship between outcome and patients' characteristics and clinical features.

For the primary endpoints, vital status at day 28 in all groups will be calculated with corresponding 95% CI. Comparison between groups will be tested using chi-square test.

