Regarding the secondary endpoints, quantitative values between groups will be compared by Student t-test or non-parametric Wilcoxon for the SOFA score (at different time points), viral load of SARS-CoV-2 (at different time points), circulating CRP (at different time points), ADL score at day 90, anxiety-depression scale at day 90, sero-conversion. Poisson regression analysis will be considered to analyse number of ventilator-free days up to day 28. Comparison of proportions will be applied to compare location of patient at day 90, as well as presence of various adverse events. If descriptive analysis revealed the presence of potential confounding factors, appropriate multivariate analysis will then be considered.

The two-sided level of significance used in this trial is 5%. Statistical analyses will be carried out using SAS (version 9.4 for Windows) statistical package.

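### Two secondary endpoints, day-90 location and acute hospital length of stay, do not account for death although 40% day-28 mortality is expected

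*Protocol*

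**What the plan says.** Day-90 location. Section 7.3 lists "location of the patients at day 90: acute care hospital, post-acute care hospital, long-term residency, home", and the synopsis gives the same four places. Section 9.9 fixes the method: "Comparison of proportions will be applied to compare location of patient at day 90". No denominator is given. The general rule in 9.9 is "Results will be analysed in intention to treat". The day-90 visit list (9.5.4.8) includes vital status but no location item. The hospital discharge list (9.5.4.10) asks, for patients alive, "Destination (Home, revalidation, acute care unit"), which is a different set of places at a different time.

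Length of stay. Section 7.2 sets the objective "to reduce the acute care hospital length of stay", so shorter is better. Section 7.3 lists "length of stay in the acute care hospital". The paragraph of 9.9 on secondary endpoints names several quantitative endpoints but not this one. What reaches it is the general sentence "Mean values between groups will be compared by Student t-test", with Wilcoxon when normality fails. The only text that links stay to death is an item for the European register in 9.5.5: "Length of hospitalisation (if no death"). It does not define the trial endpoint.

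**The concern.** Both endpoints are affected by death, and death is what plasma is meant to change.

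For location, the listed categories cannot classify every randomised patient. Comparing proportions across them conditions on being alive at day 90. If plasma saves patients who are sicker than the other survivors, those patients enter the plasma denominator and have no counterpart in the control denominator. A beneficial treatment could then look neutral or harmful on location.

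For length of stay, neither obvious reading of the default test is sound. Ending the stay at death scores an early death as a short, hence good, stay. Leaving deaths out compares survivor groups of different composition. Either way the result could mislead on a declared efficacy objective, even if mortality is reported correctly beside it.

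**Working it through.** **Inputs from the protocol.** 250 patients per arm (9.2). Control day-28 mortality is 40%, with an absolute reduction of 13.5 points (9.9), so 40 − 13.5 = 26.5% on plasma. The synopsis gives a 30% relative reduction, so 0.40 × 0.70 = 28%. I use 26.5% and show 28% where it matters. The protocol gives no figure for stay or for location, so there is no stated figure to reproduce. Stay lengths and location shares below are assumptions.

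**Patients without a location.** Control: 250 × 0.40 = 100 dead, 150 alive. Plasma: 250 × 0.265 = 66 dead, 184 alive (at 28%: 70 and 180). These are day-28 deaths, so the day-90 numbers can only be equal or higher.

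**What the denominator does to location.** Assume that plasma affects outcome only by rescuing 13.5% of its arm, that 70% of the other survivors are at home at day 90, and that a share h of the rescued are at home. The plasma home share among survivors is (0.60 × 0.70 + 0.135 × h) / 0.735. Among all randomised it is 0.60 × 0.70 + 0.135 × h, against 0.42 on control.

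| h | Survivors only, plasma minus control | All randomised, plasma minus control |
|---|---|---|
| 0.20 | 60.8% − 70% = −9.2 points | 44.7% − 42% = +2.7 points |
| 0.40 | 64.5% − 70% = −5.5 points | 47.4% − 42% = +5.4 points |
| 0.70 | 70% − 70% = 0 | 51.45% − 42% = +9.45 points |

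The sign can depend on the denominator alone.

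**Length of stay, death ending the stay.** Mean stay = p × D + (1 − p) × S, where p is mortality, D the mean stay of deaths and S that of survivors, both the same in each arm. The difference, plasma minus control, is (0.40 − 0.265) × (S − D) = 0.135 × (S − D), or 0.12 × (S − D) at 28% mortality. The last column is the share of simulated trials in which a two-sided 5% Wilcoxon test finds stay significantly longer on plasma (26.5% mortality, 250 per arm, gamma-distributed stays, coefficient of variation 1.0 to 0.5, 3,000 trials per setting).

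| D / S (days, assumed) | Shift at 26.5% | Shift at 28% | Wilcoxon favours control |
|---|---|---|---|
| 12 / 35 | +3.1 (28.9 vs 25.8) | +2.8 | 25% to 60% |
| 20 / 35 | +2.0 (31.0 vs 29.0) | +1.8 | 11% to 29% |
| 28 / 35 | +0.9 (33.1 vs 32.2) | +0.8 | 5% to 9% |
| 30 / 30 | 0 | 0 | 2% to 3% (chance level) |

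A separate set of runs gave 26% to 56%, 10% to 28%, 6% to 9% and 2%, so these shares are good to a few points only. If deaths stayed longer than survivors (35 / 30), the shift would reverse to 0.135 × (−5) = −0.7 days.

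**Length of stay, survivors only.** Let other survivors stay 35 days and rescued patients R days. The shift is 0.135 × (R − 35) / 0.735: −1.8 days for R = 25, 0 for 35, +1.8 for 45 and +4.6 for 60. The direction is not determined.

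**With death counted as the worst outcome.** For hospital-free days to day 90 with death scored zero, the difference is 0.135 × (90 − S): +8.1 days at S = 30, +7.4 at 35 and +6.1 at 45, now in favour of plasma.

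**The case against.** The strongest reply is that much of this rests on what the protocol does not say. It states no rule for deaths in length of stay, does not name that endpoint among those assigned to the t-test or Wilcoxon test, and may leave the rule to a statistical analysis plan that is not shown. This stands: it would be wrong to say that the protocol counts a death as a short stay. What the protocol does fix is the direction of benefit and a default test that has no place for death.

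A reader might infer that plasma would necessarily appear to lengthen stay. The documents do not support that. It requires deaths to be counted at their date and to precede survivors' discharges, and no stay lengths are given. The register item in 9.5.5 points, if anywhere, towards survivors only, where the bias has no fixed sign. A rejection rate near 60% is likewise the upper end of one assumed scenario.

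A reader might also infer that location will certainly be compared in survivors only. Section 9.9 gives no denominator, and under the intention-to-treat statement each location could be expressed as a share of all randomised patients. That reading is open and sound, but it is not written down, and the category list does not lead to it. Day-90 mortality is a separate endpoint, so deaths would be visible beside the location result. That helps interpretation but does not repair the comparison.

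**Conclusion.** The point holds. It is firmest for location: the protocol fixes four categories that only living patients can occupy and a comparison of proportions across them, leaving at least about 100 control and 66 plasma patients unclassified at the planning values. Those counts use day-28 mortality as a lower bound for day 90.

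For length of stay the finding is conditional. If deaths end the stay and come earlier than discharges, the mean shifts against plasma by about 0.9 to 3.1 days over the assumed gaps of 7 to 23 days, and by nothing where the stays are equal. With survivors only, the shift ranged from −1.8 to +4.6 days. All of these figures rest on assumed stays and on plasma acting through mortality alone.

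Both endpoints are secondary. The primary analysis, the sample size and the stopping rules are not touched. This is a change that should be made because it is cheap, not one on which the trial's main conclusion depends.

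**What to change.** **Location.** In 7.3 and the synopsis, add death as a fifth day-90 category. In 9.9, state that all randomised patients are compared, or that each location is a proportion of all randomised. Add a location item to the day-90 visit in 9.5.4.8, since destination at hospital discharge does not supply it. The WHO progression scale in Appendix B already ranks death as its worst score, so the approach is not new to this protocol.

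**Length of stay.** In 9.9, replace the default test by time from inclusion to discharge alive, with in-hospital death as a competing event and cumulative incidence to day 90. Hospital-free days to day 90, with death counted as zero, is an acceptable alternative. Report stay in survivors descriptively.

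**Cost.** Wording in 7.3 and 9.9, one added item at day 90, and modest analysis work. Vital status at day 90 and date of hospital discharge are already listed. The visit lists name no date of death, which the competing-event analysis needs, so its capture should be confirmed. The scoring of hospital-free days with death as zero does not need that date. The effect will no longer be a simple difference in days of stay.

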#### **9.5.4.6 Assessment visit D28 (+-1 day)**

- SOFA score calculation
- Glasgow coma score
- Peep level
- Plateau pressure
- tidal Volume
- Respiratory rate
- FiO2
- PaO2
- PaCO2
- Mean arterial pressure
- Inotropic or vasopressor support for at least one hour
  - Dopamin,
  - dobutamin,
  - noradrenalin < 0,1 µg/kg/min
  - noradrenalin > 0,1 µg/kg/min,
  - adrenalin < 0,1 µg/kg/min,
  - adrenalin > 0,1 µg/kg/min,

- vasopressin/-analogues
- Creatinin
- 24 h diuresis
- Platelet count
- Bilirubin
- CRP
- WBC count
- Ferritin
- Lymphocyte count
- Tracheal aspirate for SARS-CoV-2 viral load, expressed as cycle threshold, assessment
- Total and neutralizing antibodies to SARS-CoV-2 (centralized)

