#### **9.5.4.7 ICU discharge**

- Date of ICU discharge
- WHO progression scale

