#### **9.5.14 Premature discontinuation of trial treatment**

The treatment will be delivered as a single administration of convalescent plasma. In case of severe adverse reaction during the administration (specifically hemodynamic shock), the study plasma will be stopped, and the adverse event described and collected.

If for any reason the treatment is either not administered or prematurely stopped, the patient will remain in the trial for the intention to treat analysis.

No cross-over will be allowed.

| Procedures*                          | Visits    |           |                 |      |      |      |               |     |      |
|--------------------------------------|-----------|-----------|-----------------|------|------|------|---------------|-----|------|
|                                      | Screening | Inclusion | Treatment Phase |      |      |      | Follow Up     |     |      |
|                                      |           | D1        | D7              | D14  | D21  | D28  | ICU Discharge | D90 | D365 |
| Informed consent                     |           | x         |                 |      |      |      |               |     |      |
| Eligibility assessment               | x         | x         |                 |      |      |      |               |     |      |
| Randomisation                        |           | x         |                 |      |      |      |               |     |      |
| Medical history                      |           |           |                 |      |      |      |               |     |      |
| Comorbidities                        |           | x         |                 |      |      |      |               |     |      |
| Prior medications                    |           |           |                 |      |      |      |               |     |      |
| APACH II score                       |           | x         |                 |      |      |      |               |     |      |
| SOFA score                           |           | x         | x               | x    | x    | x    |               |     |      |
| WHO disease progression scale        |           | x         | x               |      |      |      | x             |     |      |
| CRP                                  |           |           |                 |      |      |      |               |     |      |

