## B. WHO progression scale

| OMS Progression scale         | Descriptor                                                                                                                  | Score |
|-------------------------------|-----------------------------------------------------------------------------------------------------------------------------|-------|
| Uninfected                    | Uninfected; non viral RNA detected                                                                                          | 0     |
| Ambulatory                    | Asymptomatic; viral RNA detected                                                                                            | 1     |
| Ambulatory                    | Symptomatic; Independent                                                                                                    | 2     |
| Ambulatory                    | Symptomatic; Assistance needed                                                                                              | 3     |
| Hospitalized : mild disease   | Hospitalized; No oxygen therapy                                                                                             | 4     |
| Hospitalized : mild disease   | Hospitalized; oxygen by mask or nasal prongs                                                                                | 5     |
| Hospitalized : severe disease | Hospitalized; oxygen by NIV or High flow                                                                                    | 6     |
| Hospitalized : severe disease | Intubation and Mechanical ventilation, $pO_2/FIO_2 \geq 150$ OR $SpO_2/FIO_2 \geq 200$                                      | 7     |
| Hospitalized : severe disease | Mechanical ventilation, ( $pO_2/FIO_2 < 150$ OR $pO_2/FIO_2 < 200$ ) OR vasopressors (norepinephrine $> 0.3$ microg/kg/min) | 8     |
| Hospitalized : severe disease | Mechanical ventilation, $pO_2/FIO_2 < 150$ AND vasopressors (norepinephrine $> 0.3$ microg/kg/min), OR Dialysis OR ECMO     | 9     |
| Death                         | Dead                                                                                                                        | 10    |

C. Katz Index of Independence in Activities of Daily Living

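### The last WHO progression score is taken at ICU discharge, a time set by recovery; scoring the scale at the existing day-28 visit would give a second fixed-time comparison at little cost

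*Protocol*

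**What the plan says.** **Endpoint list (Protocol 7.3).** The scale is a secondary endpoint at three times: "WHO progression scale prior transfusion, at day 7 and at discharge (see appendix B". The kind of discharge is not named.

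**Visits (9.5.4).** The scale is an item at inclusion (D1) and at D7. It is not an item at D14, D21, D28 or D90. The ICU discharge visit (9.5.4.7) has two items only: "Date of ICU discharge" and "WHO progression scale". The hospital discharge visit (9.5.4.10) records "Date of hospital discharge", other dates, destination and tracheostomy, but not the scale.

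**Flow chart (after 9.5.14).** The row "WHO disease progression scale" is marked at D1, D7 and ICU discharge only.

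**Scale (Appendix B).** It runs from 0 to 10. Intubated patients score 7, 8 or 9, and death scores 10. Scores 8 and 9 depend partly on "vasopressors (norepinephrine $> 0.3$ microg/kg/min".

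**Day-28 data.** The D28 visit (9.5.4.6) already collects PaO2, FiO2 and vasopressor use, and the flow chart adds ventilation, renal replacement and ECMO. Section 9.6.1 plans visits at days 7, 14, 28 and 90 for patients who have left hospital.

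**The concern.** Every patient is intubated at entry (9.3.1) and so starts at 7, 8 or 9. Leaving the ICU alive generally means having come down from those steps. A score taken at that moment is largely fixed by the event that triggers it. A patient who leaves early and one who leaves late can receive the same score, so a treatment that speeds recovery need not show.

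What is at stake is one of the two post-baseline assessments of a secondary endpoint. As scheduled, the scale cannot be compared between arms at any common time after day 7, although the trial's main horizon is day 28 and patients are visited then.

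**Working it through.** The protocol gives no figure for this endpoint, so there is none to reproduce. The check has three parts.

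**1. Which discharge.** Section 7.3 leaves it open. Section 9.5.4.7 and the flow chart place the scale at ICU discharge, and 9.5.4.10 omits it at hospital discharge. ICU discharge is therefore what will be collected.

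**2. What a discharge-timed score can show.** This is an illustration.

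From the protocol: 250 per arm, control mortality 40%, intervention mortality 40% − 13.5% = 26.5% (9.9).

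Assumed:
- survivors leave the ICU at score 4, 5 or 6 with probability 0.2, 0.6, 0.2 in both arms;
- ICU stay of survivors is log-normal, median 20 or 14 days, log-SD 0.6;
- time of death is log-normal, median 12 days, log-SD 0.7;
- patients still in the ICU score 7, 8 or 9 with probability 0.40, 0.35, 0.25;
- a patient out of the ICU keeps the exit score at the fixed day.

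Share of survivors out of the ICU by day d = Φ(ln(d / median) / 0.6):
- day 14: Φ(ln(14/20)/0.6) = Φ(−0.594) = 0.276 v Φ(0) = 0.500;
- day 28: Φ(ln(28/20)/0.6) = Φ(0.561) = 0.713 v Φ(ln(28/14)/0.6) = Φ(1.155) = 0.876.

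With 40% mortality in both arms, the difference among all patients is 0.6 × (0.500 − 0.276) = 0.134 at day 14 and 0.6 × (0.876 − 0.713) = 0.098 at day 28. At ICU discharge it is zero by definition, because every survivor is scored on leaving.

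Share of 2,000 runs with two-sided Wilcoxon P < 0.05 (the day-28 column is a separate set of 2,000 runs of the same model):

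| Scenario | At ICU discharge, survivors | At ICU discharge, death = 10 | Fixed day 14 | Fixed day 28 |
|---|---|---|---|---|
| Mortality 40% v 40%, median stay 20 v 14 days | 5.0% | 4.5% | 50% | 24% |
| Mortality 40% v 26.5%, stay 20 days in both | 5.2% | 79% | 46% | 73% |
| No difference | 5.3% | 4.7% | 4.9% | 5.5% |

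The discharge score responds only when mortality differs and deaths are counted. That contrast is already the primary endpoint, for which a fixed-sample comparison of 40% v 26.5% with 250 per arm has about 90% power.

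**3. Whether the score can be checked from recorded data.** The D7 form splits noradrenaline at 0.1 µg/kg/min, the cut used by SOFA (Appendix A). The D28 form has the same band, "noradrenalin > 0,1". Enumerating Appendix B without dialysis or ECMO:

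| PaO2/FiO2 | Band below 0.1 | Band above 0.1 |
|---|---|---|
| 150 or more | 7 | 7 or 8 |
| below 150 | 8 | 8 or 9 |

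Dialysis or ECMO gives 9 at any dose. The upper band thus leaves the score open by one category. This reads score 8 by its limit of 150. As printed, its second limb repeats pO2/FIO2 with a limit of 200, which overlaps score 7 between 150 and 199 and should be reconciled.

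**The case against.** **The arms can still be compared.** A reader might infer that the scale cannot compare the arms at all. The protocol does not support that. Day 7 is a fixed-time comparison, and Appendix B gives death a score of 10, so a discharge score with deaths included can differ between arms (79% in the illustration). What stands is narrower: that difference comes from mortality.

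**The survivor restriction belongs elsewhere.** The wording "At discharge (if the patient survives" is in 9.5.5, the data set for the European register. The endpoint in 7.3 carries no such restriction, and how deaths enter the score may properly be left to the SAP. A survivors-only analysis is therefore a possibility, not something the protocol states.

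**Day 28 is not empty.** It would be wrong to say that the trial has no ordinal status then. SOFA is an endpoint at days 7, 14 and 28, and ventilator-free days and hospital stay capture part of the timing of recovery. This lowers the stakes, but does not make the discharge score informative.

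**The noradrenaline bands do not block scoring.** The scale is its own recorded item at D1, D7 and ICU discharge. Nothing says it is computed from the bands, and an investigator with the chart can apply the 0.3 limit. The bands only limit later checking at day 7, in patients above 0.1 without dialysis or ECMO.

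**The simulation builds in its premise.** Equal exit scores in both arms are assumed, so the 5% in survivors illustrates the mechanism and does not prove it. If treatment changed the condition in which patients leave, the discharge score would show some of that. This is a fair limit on the figures.

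**Conclusion.** The point holds as a better-timed version of a listed secondary endpoint. The last WHO score falls at a post-randomisation time set by recovery. In survivors it largely reflects fitness to leave the ICU, with deaths scored 10 it mainly repeats mortality, and only day 7 offers a fixed-time comparison after baseline.

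The size is illustrative. Under the stated assumptions, a shortening of median ICU stay from 20 to 14 days with equal mortality is invisible to the discharge score (about 5%), but is detected in about 50% of runs at day 14 and 24% at day 28. The gain at day 28 is real but modest, because most survivors have left the ICU by then. The model also omits the spread that scores of 1 to 3 for patients already home would add. The protocol gives no ICU-stay distribution, so these percentages should not be read as the trial's power.

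The wording on baseline is a minor matter. Controls receive no plasma, so a pre-transfusion score does not apply to them, but the D1 item already supplies a baseline for both arms.

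The scale is absent from the synopsis endpoints and is not named in the analyses of 9.9. The primary endpoint, sample size and stopping rules are unaffected.

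**What to change.** - Score the scale at the existing D28 visit in all randomised patients, with death = 10 as in Appendix B. Score patients already discharged at the day-28 contact that 9.6.1 plans.
- Name day 7 and day 28 as the between-arm comparisons.
- State in 7.3 that the discharge meant is ICU discharge, and keep that score as descriptive only.
- State that baseline is D1 for both arms.
- Optional: record the actual noradrenaline dose, or add a split at 0.3 on the data form, so that the day-7 score can be verified. This helps because treatment is open label (9.4.4).
- Optional: take the score at the D14 visit too, where the illustration shows the larger gain for speed of recovery.

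The cost is one further eCRF item at a visit that already collects most of the components, and a short contact for patients at home by day 28. The noradrenaline option adds one field or category.
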